### Measures

This longitudinal observational study will collect a wide range of self-reported, physiological, and other sensor data. The measures relating to the primary outcomes will be described first, followed by EMA measures, wearable measures, and other self-reported data.

#### Primary outcomes

For Aim 1, acceptability, feasibility, adherence, and usability will be measured using a mixed methods approach. Acceptability and usability will be collected from participants at Time 3, using quantitative self-report measures of ease of use (1; Very Difficult to 5; Very easy), ease of understanding (1; Very Difficult to 5; Very easy), and levels of frustration with the study protocol (1; Very Frustrating to 5; Not at all), as well as qualitative responses to strengths and limitations of the protocol. Feasibility and adherence will be determined using missing data patterns for both wearable and EMA data, and number of support calls required.

For Aim 2, an EMA measure of anger intensity (*Rate the overall intensity of the anger or irritability you feel right now*; 10-point Likert Scale ‘1’ Lowest intensity; ‘10’ Highest intensity), and wearable data related to physiological indictor of stress (1–100) will be used (see sections below for more details).

#### EMA measures

EMA measures of anger intensity, frequency, verbal aggression, physical aggression, pain, sleep, alcohol use, and rumination will be collected (Table 2). EMA measures will be delivered approximately every four hours with an individualised schedule. Participants will be asked to nominate their daily waking time prior to study commencement, and the first daily EMA is randomised to occur within the one hour of the waking window. From there, the second, third and fourth EMA surveys for the day occur at randomised four hourly intervals. EMA measures are delivered to the individual’s smartphone via the mEMA-sense platform.

**Table 2 pone.0278926.t002:** Overview of EMA measurements.

Construct	Item wording	Scale type	Prompting time			
			1	2	3	4
Anger-related rumination	*In the past 3 hours I kept thinking about events that had angered me*	4-point Likert Scale	✓	✓	✓	✓
		(‘1’ Almost Never to ‘4’ Almost always)				
Pain	*How much pain are you currently experiencing*?	Visual analogue scale	✓	✓	✓	✓
		[no pain] to [worst pain imaginable]				
Alcohol consumption	*In the past 3 hours*, *how many standard drinks containing beer*, *wine*, *liquor*, *or any other alcohol did you consume*?	8-point Likert Scale	✓	✓	✓	✓
		*(‘0’ No drinks to ‘7’ 7+ drinks)*				
Sleep quality	*During the past night*, *how would you rate your sleep quality overall*?	4-point Likert Scale	✓			
		(‘*0’ Very good; ‘1’Fairly good; ‘2’ Fairly bad; ‘3’ Very bad*)				
Nightmares	*During the past night*, *how distressing were your dreams or nightmares*?	5-point Likert Scale	✓			
		(‘*0’ No dream or not at all distressing; ‘1’ Slightly distressing; ‘2’ Somewhat distressing; ‘3’ Very distressing; ‘4’ Extremely distressing*				
Anger intensity	*Rate the overall intensity of the anger or irritability you feel right now*.	10-point Likert Scale	✓	✓	✓	✓
		*‘1’ Lowest intensity; ‘10’ Highest intensity*				
State anger frequency/duration	*In the past 3 hours*, *how much of the time did you feel angry or irritable*?	5-point Likert Scale	✓	✓	✓	✓
		(‘*0’ Never; ‘1’ Little; ‘2’ Somewhat; ‘3’ Much; ‘4’ A great deal*)				
Anger expression #1	*When you felt angry or irritable over the past 3 hours*, *to what degree did you speak or shout about your anger or irritability*?	5-point Likert Scale	C✓	C✓	C✓	C✓
		(‘*0’ Never; ‘1’ Little; ‘2’ Somewhat; ‘3’ Much; ‘4’ A great deal*)				
Anger expression #2	*When you felt angry or irritable over the past 3 hours*, *to what degree did you do physical things like gesture*, *pound the table*, *slam doors*, *throw things*, *and so forth*?	5-point Likert Scale	C✓	C✓	C✓	C✓
		(‘*0’ Never; ‘1’ Little; ‘2’ Somewhat; ‘3’ Much; ‘4’ A great deal*)				

#### Wearable data

Wearable outcomes will include heart rate, inter-beat interval, stress, daily steps per day, and GPS location at the time of the EMA prompt. The key wearable variable of interest for Aim 2 is stress.

#### Demographic and mental health measures

In addition to EMA and wearable data, self-report measures for pre- and post-ambulatory assessment will be collected. These are presented in Table 3.

**Table 3 pone.0278926.t003:** Overview of pre- (Time 1) and post- ambulatory assessment (Time 3) measures.

Time point(s)	Construct	Measure
Time 1	Demographic information	Gender, age, relationship, employment, treatment information
Time 1; Time 3	Problem anger	Dimensions of Anger Reactions Scale-5 (DAR-5; a cut-off of ≥12).
Time 1; Time 3	State and trait anger	State-Trait Anger Expression Inventory 2 (STAXI-2)
Time 1; Time 3	Pain	Visual analogue scale (VAS)
Time 1; Time 3	Posttraumatic stress disorder symptoms	Posttraumatic Stress Disorder Checklist (PCL-5)
Time 1; Time 3	Emotional self-awareness	Emotional Self Awareness Scale (ESAS)
Time 1; Time 3	Anger rumination	Anger Rumination Scale (ARS)
Time 1	Trauma exposure	Life Events Checklist for DSM-5 (LEC-5)
Time 1	Sleep disturbances	Insomnia Severity Index (ISI)
Time 1	Alcohol use	Alcohol Use Disorders Identification Test-Concise (AUDIT-C)

#### Data collection and management

Data will be collected through three channels, including REDCap for pre- and post-study surveys, wearable sensors, and smartphones. Wearable data will be transferred via Bluetooth to the individual’s smartphone, and smartphone data will then be pushed to the cloud-based platform ilumivu (ilumivu, Asheville, NC). Data in this platform is encrypted and anonymised and will be downloaded into the local database once data collection is finished. Access to both cloud and local databases is password-protected so entry is permitted to study investigators only.

#### Safety considerations

During the EMA assessment period, participants will be prompted on a regular basis to consider their anger and aggression. Previous research in this population indicates that regular prompting does not increase distress or anger [11]. To mitigate risk of working with individuals at significant risk of violence to others, individuals are screened out if they have recently used significant violence (i.e., resulting in injury to others, used a weapon, and/or used choking in the past six months). In addition, the study employs a clinical psychologist and psychiatrist who oversaw the development of a risk management plan for participants to monitor and manage risk of harm to self and others.

#### Statistical analyses

For Aim 1, descriptive analyses of quantitative measures of acceptability, feasibility, adherence, and usability will be conducted and mean, range and median responses to questions reported. Qualitative data collected from interviews with participants will be synthesised.

For Aim 2, continuously measured physiological stress (Garmin formula [17]; score 1–100) captured by wearable sensors will be examined as a predictor of self-reported anger intensity (1–10). Values recorded in the 10-minute interval prior to the EMA micro-survey will be extracted for use in the prediction models.

Descriptive analyses will be performed on the data to determine missingness, completion rates, outliers and erroneous values, and a proxy for wear time of the wearable sensor, e.g. time between first and last values each day [18]. The following analysis methods that can handle predictors that have been continuously measured prior to each longitudinal outcome measurement will be considered: i) two-stage approaches where appropriate features (maximum, variance, etc.) of the continuously measured predictors are included in a generalised linear mixed model [18–20]; ii) functional data analysis (FDA) approaches, where the continuously measured predictors are treated as functions when building prediction models [21]. FDA can be implemented in either regression modelling frameworks [22] or machine learning frameworks, such as functional partial least squares [23] and random forests [24]. The predictive performance of each model will be assessed using the balanced error rate (percentage of misclassified momentary anger episodes) calculated using 5-fold cross-validation. Variables importance will also be assessed using metrics suitable for the modelling approach [25].

Additional models, including Dynamic Structural Equation Models (DESM) and Time Varying Effects Models (TVEM), will be built to investigate bi-directional relationships between anger and variables of pain, alcohol, sleep quality, and rumination. Data cleaning and statistical analyses will be performed in SPSS (v23, IBM) and R (R. RStudio, Boston, MA, USA; [26].

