Digital mental health interventions offer promise to individuals with problem anger. Recent research has shown that CBT principles can be effectively delivered via smartphone to individuals with problem anger [10], and that longitudinal smartphone-based studies are feasible in individuals with problem anger [11]. Previous research in problem anger has also shown that anger varies frequently on a moment-to-moment basis and, like other affective states, is ecologically influenced. This creates an opportunity for personalised digital interventions such as just-in-time adaptive interventions [12], which have the goal of delivering support “at the moment in the context that the person needs it most and is most likely to be receptive [13]”. In addition to smartphone delivery, modern technology can facilitate multimodal ambulatory assessment and peripheral physiology metrics that can integrate detailed self-report data via ecological momentary assessment with objective, passively collected sensor data through smartphones and wearables. The combined data may provide rich, ecologically valid, contextual, and biopsychosocial information about mental health issues, including temporal information about the dynamics of psychological phenomena [14]. As such, there is the potential for wearable technology to be leveraged to reliably predict and subsequently alter mood states [15]. Given the preliminary findings relating to the potential for digital mental health to address problem anger, coupled with advances in wearable and smartphone technology, the primary aims of this study are to:

Investigate the feasibility and acceptability of the use of a commercial wearable to capture physiological data in a trauma-affected population.Determine whether high levels of self-reported anger intensity can be predicted from physiologically measured stress.

Secondary aims from this study will be exploratory in nature. We will examine relationships among common associated features of problem anger such as pain, alcohol use, sleep, and anger rumination, as well as physiological variables collected from the wearable such as heart rate, inter-beat-interval, location, and steps. The findings from this study will provide world-first evidence for the feasibility of ambulatory assessment (i.e., smartphone and wearable) of physiological and emotional aspects of dysregulated mood in trauma-affected individuals, to inform the development of digital mental health tools.

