### Power and sample size

The total feasible sample size is ~100 participants due to the expense of wearables. Specific sample size details for Aim 1 and 2 are described below.

For Aim 1, a target of a minimum of 75% of participants reporting satisfaction with ease of use of the wearable and app, and low frustration is set. A total feasible sample size of 100 participants would ensure that the precision of the two-sided 95% confidence interval of the true underlying proportion of participants who adhere to the intervention is at most +/- 9% when assuming a proportion of 75% using the Wald method to measure the 95% confidence interval.

For Aim 2, a sample size of 100 participants provides a total of 4000 possible outcome observations since each participant has 40 measurement occasions. It is assumed that up to 30% of these observations will be missing [11], resulting in 2800 possible observations (approximately 28 per participant) and that 25% of recorded outcomes will be high intensity anger (≥ 7). The design effect is estimated to be 14, assuming an intraclass correlation of 0.48 from prior data, which leads to an effective sample size of 200 for this study if 100 participants are recruited. Sample size calculations for prediction modelling were conducted according to the three criteria (shrinkage, overfitting and precision; [16]. An effective sample size of 200 results in the ability to detect a minimum Cox-Snell R^2^ of approximately 0.04 assuming one predictor (physiologically recorded stress; 1–100) and ensuring the shrinkage is the recommended 0.9. This sample size satisfies the overfitting criteria for a maximum possible Cox-Snell R^2^ of 0.53, according to estimates of the null model log-likelihood and provides a margin of error of 0.06, marginally higher than the more stringent 0.05 but below the required 0.1.

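### One overall balanced error rate is the only performance measure for every Aim 2 model, so ranking people by usual stress could be reported as prediction of a person's angry moments

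*Protocol article*

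**What the plan says.** Aim 2 in the Introduction is to "Determine whether high levels of self-reported anger intensity can be predicted from physiologically measured stress". The same section motivates the study by just-in-time interventions, described through a cited source as support "at the moment in the context that the person needs it most". The Discussion says the answers will inform such tools.

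On clustering, Power and sample size states: "The design effect is estimated to be 14, assuming an intraclass correlation of 0.48 from prior data". It allows 40 occasions per person, 30% missing, and 25% of recorded outcomes at high intensity (7 or more).

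For the models, Statistical analyses says that "analysis methods that can handle predictors that have been continuously measured prior to each longitudinal outcome measurement will be considered". Option (i) takes features of the stress signal, which "are included in a generalised linear mixed model". Option (ii) is functional data analysis, by regression or by "machine learning frameworks, such as functional partial least squares [23] and random forests [24". The stress input is what the wearable recorded in the ten minutes before each prompt. One scoring rule then covers all options: "The predictive performance of each model will be assessed using the balanced error rate (percentage of misclassified momentary anger episodes) calculated using 5-fold cross-validation". No per-participant measure of performance is named.

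**The concern.** A stress reading can be linked to a high anger score in two ways. People whose stress score is usually high may be people who are usually angry (between persons). Or stress may rise above a person's own level when that person is angry (within person). A just-in-time tool needs the second, because it must decide when to act for a given user. An error rate taken over all episodes rewards both and does not show which one earned the reward.

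Splitting folds by participant does not solve this. A between-person association is a real feature of the population and carries over to new participants. A comparison with a model without stress does not expose it either, because stress does add information about who is angry. Aim 2 could therefore end with the statement that stress predicts momentary anger when it has only sorted people.

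**Working it through.** **The plan's own clustering figures**

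- Records: 100 × 40 = 4000; less 30% missing = 2800, or 28 per person.
- Design effect: 1 + (28 − 1) × 0.48 = 13.96 (stated: 14).
- Effective sample size: 2800 / 13.96 = 200.6 (stated: 200).

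Both reproduce, so the plan's inputs do imply large differences between people in how often they are highly angry.

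**Can the overall error rate fall with no within-person link?**

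Inputs from the article: 100 people, 28 records each, 25% high anger, ICC 0.48.

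Assumptions not in the article:
- a normal latent anger score cut at 7 or more, with latent ICC 0.712 so that the binary outcome has ICC 0.48;
- a stress ICC of 0.1, 0.3 or 0.5;
- a between-person stress-anger correlation of 0, 0.2 or 0.4;
- a within-person stress-anger correlation of exactly 0;
- a linear classifier on uncentred stress, cut at the prevalence, standing in for the candidate models.

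Balanced error rate = ½ × (share of high records called low + share of low records called high), so 0.50 is chance. Folds were split by participant. The overall rate uses all records. The within-person rate is computed for each participant who has both high and low records, then averaged.

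| Between-person correlation | Overall error, stress ICC 0.1 / 0.3 / 0.5 | Within-person error |
|---|---|---|
| 0 | 0.50 / 0.50 / 0.50 | 0.50 |
| 0.2 | 0.487 / 0.473 / 0.463 | 0.50 |
| 0.4 | 0.465 / 0.440 / 0.419 | 0.50 |

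Under the same assumptions about 32% of participants have no high record and 2% have only high records. About 65% have both and enter the within-person rate.

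**Does this depend on the classifier or the ICC scale?**

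A second simulation used the best single cut-point and read 0.48 on the latent scale, with stress ICC 0.5 and participant-level folds. Overall error was 0.500, 0.455, 0.422 and 0.387 at between-person correlations 0, 0.3, 0.5 and 0.7. The within-person area under the curve stayed at 0.50. Centring stress on each person's mean returned the error to 0.50.

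**Does the measure also mislead the other way?**

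Yes. With a within-person correlation of 0.3 and no between-person link, overall error is 0.45-0.47 while within-person error is 0.40-0.43. The overall figure then understates what stress can do for a given person.

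**The case against.** A reader might infer that functional partial least squares and random forests will treat the 2800 records as independent. The article does not say so. The methods are only to be considered, the two are given as examples, and the whole set is introduced as suited to longitudinal outcomes. How the person is modelled may be set out in the full plan or in the cited methods papers, so no finding rests on that silence.

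A reader might also infer that the fault belongs to machine learning. It does not. The mixed model is scored on the same overall figure, and a random intercept does not by itself separate a person's usual stress from deviations around it.

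It is also tempting to say that a between-person difference would pass as prediction. 'Could' is the most that holds. The effect needs a between-person correlation that the article does not give, and at zero correlation with participant-level folds there is none. The smallest case, 0.487, is barely below chance, and the article sets no rule that any value under 0.50 counts as success. Neither functional partial least squares nor a random forest was simulated.

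Finally, Aim 2 as worded does not say within-person, and the just-in-time definition is background from a cited source. That is fair: overall prediction is a legitimate result to report. But the Discussion ties the answer to just-in-time tools, and for that use the overall figure alone is not enough. Nor is this only a detail left to a fuller plan, since the performance measure is what the article does fix.

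**Conclusion.** The point holds as a limit of the stated performance measure, for every candidate model. With the plan's clustering and no within-person link, overall balanced error could fall from 0.50 to about 0.49-0.42 while within-person error stays at 0.50. This rests on an assumed between-person correlation of 0.2-0.4, an assumed stress ICC of 0.1-0.5, and a simple classifier standing in for the candidates. The document supports none of the stronger readings: that the models are stated to ignore clustering, that machine learning is the cause, or that false prediction is bound to occur. It is an inexpensive improvement that makes the Aim 2 result interpretable for its stated use. It is not an error that invalidates the analysis.

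**What to change.** In Statistical analyses, for every Aim 2 model:

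1. Keep the overall balanced error rate and report beside it a within-participant rate: computed per participant among those with both high and low records, then averaged, with an interval from resampling participants.
2. Base any statement that stress predicts momentary anger on the within-participant figure.
3. Enter stress as two terms, the participant's own level and the deviation from it. If the model is to represent real-time use, take the level from earlier records or a run-in. A mean over all ten days would use readings made after the moment being predicted and would not exist for a new user.

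The cost is wording and some code. About a third of participants (32% + 2% = 34% under the assumptions above) have only low or only high records and do not enter the within-participant figure. Others contribute few high records, so it is less precise than the overall one. The reported performance may also look less favourable.

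### The parenthesis that defines the balanced error rate, the only predictive-performance measure named for Aim 2, describes a different quantity

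*Protocol article*

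**What the plan says.** One of the two primary aims in the Introduction is to find out whether high self-reported anger intensity can be predicted from wearable-measured stress. The Statistical analyses section lists several candidate approaches: mixed models on extracted features, functional regression, functional partial least squares and random forests. Each model is to be assessed by the "balanced error rate (percentage of misclassified momentary anger episodes"), "calculated using 5-fold cross-validation". Variable importance is also mentioned, but it does not measure predictive performance, and the article names no other measure that does.

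The Power and sample size section supplies the outcome split. It assumes that "25% of recorded outcomes will be high intensity anger (≥ 7"), with missing data "resulting in 2800 possible observations (approximately 28 per participant").

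**The concern.** The sentence names one measure and defines another. The balanced error rate gives the high-anger and the other records equal weight, whatever their numbers. The parenthesis does not average over two classes. Taken literally, its denominator is the anger episodes alone, so it counts missed episodes and ignores false alarms. Taken loosely, its denominator is all records, so the larger class dominates.

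This measure ranks the candidate models and answers a primary aim. The miss rate rewards flagging too much, and the overall error rewards flagging too little when high anger is the minority class. Two analysts working from the same sentence, one from the name and one from the parenthesis, could choose different models and report different conclusions about whether stress predicts anger.

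**Working it through.** **Inputs** (Power and sample size section): 2800 expected records, about 28 per participant; 25% high anger, defined as a score of 7 or more; intraclass correlation 0.48; design effect 14; effective sample size 200; minimum Cox-Snell R² about 0.04. I take 7 or more as the class boundary for the error rates, because it is the only one the article gives.

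**The plan's own figures reproduce.**
- Design effect: 1 + (28 − 1) × 0.48 = 13.96 (stated 14).
- Effective sample size: 2800 / 14 = 200 (stated 200).
- Margin of error: 1.96 × √(0.25 × 0.75 / 200) = 0.060 (stated 0.06).
- R² at shrinkage 0.9: 0.9 × (1 − exp(−1 / (0.1 × 200))) = 0.044 (stated about 0.04).

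The 25% share is therefore the figure the design works with.

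**The three quantities.** There are P = 0.25 × 2800 = 700 high-anger records and Q = 2100 others. FN is the number of missed high-anger records and FP the number of false alarms.
- Miss rate (literal reading) = FN / P
- Overall error (loose reading) = (FN + FP) / (P + Q)
- Balanced error rate = ½ × (FN / P + FP / Q)

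**Rules that use no information:**

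| Rule | FN | FP | Miss rate | Overall error | Balanced error |
|---|---|---|---|---|---|
| Flag nothing | 700 | 0 | 100% | 25% | 50% |
| Flag everything | 0 | 2100 | 0% | 75% | 50% |
| Flag a random 25% | 525 | 525 | 75% | 37.5% | 50% |

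In general, flagging a random fraction q gives a miss rate of 1 − q, an overall error of 0.25(1 − q) + 0.75q = 0.25 + 0.5q, and a balanced error of ½(1 − q + q) = 50%. The literal reading is best at q = 1 and the loose reading at q = 0. Only the balanced error is the same for every useless rule. This step needs no modelling assumption beyond the 25% share.

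**Illustration that the definition can reverse a ranking.** Assumptions, not in the article: a marginal logistic model, one normally distributed predictor, no participant effect, R² = 0.044, and two assumed probability cuts.

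| Cut | Sensitivity | Specificity | Overall error | Balanced error |
|---|---|---|---|---|
| 0.50 | 2.4% | 99.3% | 24.9% | 49.1% |
| 0.25 | 59.8% | 59.7% | 40.3% | 40.2% |

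Overall error prefers the first row, which flags almost nothing. Balanced error prefers the second. The reversal persists at R² = 0.10 (overall 23.9% v 35.1%; balanced 44.4% v 35.0%) and at R² = 0.20 (overall 20.9% v 28.3%; balanced 35.5% v 28.1%).

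**The case against.** The strongest reply is that the balanced error rate is an established term with one standard meaning, that it suits an outcome with a 25% share, and that the parenthesis is a lay gloss in a condensed article. An analyst who computes the named measure gets the right number. The first two parts stand, and they are why the measure should be kept. But the parenthesis is the only definition printed, and it matches two other measures in real use, each of which favours a useless rule here. An unseen analysis plan may add detail, but it would not make this sentence correct.

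A reader might go further and infer that the plan will miss a real signal, because at a default cut of 0.5 a weak model has a balanced error near 50%. The article does not support that, for three reasons.
- It states no cut, and leaving the cut to the analysis plan is not an error.
- R² of about 0.04 is the minimum the sample size allows for, not the expected effect. At R² = 0.30 the same calculation gives a balanced error of 27.7% at the 0.5 cut.
- The calculation ignores participant effects, although the article works with "assuming an intraclass correlation of 0.48 from prior data" and lists a mixed model as an option. In a simulated random-intercept logistic model (latent-scale intraclass correlation 0.48, within-person slope 0.51, 22 training and 6 held-out records per participant), about 17% of records are flagged at the 0.5 cut, and the balanced error is about 30%, or 24% at the 0.25 cut.

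Those lower errors come almost wholly from the participant intercept, being nearly the same with a slope of zero, so they are not evidence of a stress signal either. They apply only if a participant's records fall in both training and test folds, which the article does not say.

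Replacing the balanced error rate with AUC as the main measure would be a preference, not a correction.

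**Conclusion.** The point holds for the definition. The parenthesis is not the balanced error rate on either reading. At the article's own 25% share, a useless rule can score 0% on one reading and 25% on the other, against a true balanced error of 50%. If the parenthesis is followed, model choice and the Aim 2 conclusion can be wrong; if the named measure is computed in its standard form, they are not affected by this fault. The result rests on the 25% share and the boundary of 7, both from the sample-size section. The figures tied to a 0.5 cut illustrate how the definitions can disagree and are not a property of the plan.

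**What to change.** Replace the parenthesis with: the mean of the false-negative rate in records with anger of 7 or more and the false-positive rate in records with anger below 7. Keep the balanced error rate as the performance measure and state that 50% is its no-information value. Report sensitivity and specificity beside it, so that a reader can see which class the errors fall in, and the cross-validated AUC, which does not depend on a probability cut.

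This changes wording only and needs no new data. The one downside is a little more reporting. At the time of writing about 15% of the desired sample had completed the study, so the definition could be settled well before the Aim 2 models are compared.

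### Aim 2 is judged on an absolute cross-validated error rate, with neither participant-level folds nor a no-stress reference model specified, so a model that knows nothing about stress can appear to predict anger

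*Protocol article*

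**What the plan says.** The second primary aim is to determine whether high self-reported anger intensity can be predicted from physiologically measured stress.

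**Statistical analyses.** Several model families are to be considered. The first is a two-stage approach in which summary features of the stress signal "are included in a generalised linear mixed model". The others are functional regression, functional partial least squares and random forests. Each model is assessed by its balanced error rate, which a parenthesis describes as the percentage of anger episodes misclassified, "calculated using 5-fold cross-validation". Variable importance is to be assessed as well, by a metric that is not named. The section states no unit for the folds, no model without stress and no benchmark error rate.

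**Power and sample size.** The same data are treated as strongly clustered: "a sample size of 100 participants provides a total of 4000 possible outcome observations since each participant has 40 measurement occasions", then 30% missing, "resulting in 2800 possible observations (approximately 28 per participant"), and an expectation that "25% of recorded outcomes will be high intensity anger (≥ 7"). The clustering enters by "assuming an intraclass correlation of 0.48 from prior data". "The design effect is estimated to be 14", "which leads to an effective sample size of 200 for this study if 100 participants are recruited".

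**The concern.** The sizing treats records from one person as highly dependent. The validation sentence does not carry that dependence forward. If the folds are drawn over records, nearly every held-out record has many records from the same person in the training set. A mixed model that uses its estimated random intercept then predicts the held-out rating largely from that person's own other anger ratings. The error rate falls because the model knows who is usually angry, whether or not stress carries information.

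The only stated performance criterion is each model's own error rate, so it would not show the difference. The study could report that a wearable predicts anger when stress contributed nothing. This bears on a primary aim, and the Discussion says the answer will inform just-in-time interventions.

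**Working it through.** **1. Inputs (Power and sample size).** 100 participants; 28 records each after 30% missing; 25% of outcomes high; ICC 0.48. The article does not say whether the ICC refers to the 1–10 score or to the binary outcome, so both scales are shown.

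**2. The plan's own figures reproduce.**
- Design effect = 1 + (28 − 1) × 0.48 = 13.96, stated as 14.
- Effective sample size = 2800 / 13.96 = 200.6, stated as 200.

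**3. What record-level folds reveal about a person.** With 5 folds, each person has on average 28 × 4/5 = 22.4 records in the training set. At ICC 0.48 for the outcome being averaged, the reliability of that person's training mean is 22.4 × 0.48 / (1 + 21.4 × 0.48) = 10.75 / 11.27 = 0.95. The person's usual anger level is therefore almost fully known when the held-out records are predicted.

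**4. Simulation with no stress information.** 300 data sets of 100 × 28 binary outcomes with mean 0.25. Under record-level folds, the prediction is the participant's shrunken (empirical-Bayes) rate from the training folds only. Under participant-level folds, it is the training prevalence. A record is classed as high at a predicted probability of 0.25 or of 0.5.

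| Participant effect | Balanced error, cut 0.25 | Balanced error, cut 0.5 | AUC |
|---|---|---|---|
| Binary ICC 0.48, beta-binomial | 0.176 | 0.221 | 0.903 |
| Binary ICC 0.48, normal intercept (latent ICC 0.71) | 0.178 | 0.221 | 0.902 |
| Latent ICC 0.48, logit-normal | 0.250 | 0.315 | 0.824 |
| Latent ICC 0.48, normal intercept (binary ICC 0.29) | 0.261 | 0.331 | 0.816 |
| Latent ICC 0.20, normal intercept | 0.370 | 0.462 | 0.679 |
| ICC 0 | 0.500 | 0.500 | 0.500 |

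A repeat run gave 0.17–0.22 on the binary scale and 0.25–0.32 on the latent scale. The rows for ICC 0.20 and 0 show that the effect comes from the clustering.

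With participant-level folds, the empty model has a balanced error of 0.50 at cut 0.5. At cut 0.25 it is 0.52 to 0.53: the training prevalence falls on either side of the cut, and in the opposite direction to the prevalence in the held-out fold.

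**5. If the parenthesis is read as the raw percentage misclassified.** Always predicting not-high already scores 25%, however the folds are formed. The no-stress intercept model under record-level folds scores 0.145 (binary ICC 0.48) or 0.199 (latent ICC 0.48) at cut 0.5.

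**6. Machine learning on stress features alone.** Random forest on four pure-noise features with person-specific levels and no participant identifier; binary anger ICC 0.48; 8 replicates. The article gives no ICC for stress, so the range is an assumption.

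| Assumed stress ICC | Balanced error, record-level folds | Balanced error, participant-level folds |
|---|---|---|
| 0 | 0.50 | 0.50 |
| 0.3 | 0.48 | 0.50 |
| 0.5 | 0.46 | 0.50 |
| 0.7 | 0.42 | 0.50 |

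A smaller run with three features, stress ICC 0.7 and 4 replicates gave 0.44 against 0.49. The leak is real here but modest.

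**The case against.** The strongest reply is that the text is silent on this, not wrong. A reader might infer that the folds are split by record. The article does not say so, and participant-level folds fit its wording equally well. A journal article may leave fold construction to a fuller plan, and the authors show in the sizing that they know the clustering matters. That stands, and the point does not rest on claiming that the folds are ungrouped.

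A reader might also infer that any Aim 2 model would look good without stress. The documents do not support that either. The large artefact needs record-level folds together with predictions that use participant effects. It is small for stress-only random forests. With fixed-effect-only predictions it is absent unless stress values identify the person. The mixed model is one of several candidates.

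Two further replies have partial force. Variable importance bears on whether stress contributes, but with no metric named it does not replace a comparison with a model that knows only the participant. And a true balanced error rate has a built-in chance value of 0.50, so under participant-level folds the missing reference model matters less. It matters more if the raw percentage is meant.

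Using a person's own outcomes is also not wrong in itself, since the Introduction mentions personalised interventions. In that case the relevant question is what stress adds to the person's own history, which again requires the no-stress comparison.

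What remains is more than missing detail. The article does fix the metric and the validation scheme. An ordinary reading of them, with the first-listed model, can give a false positive answer to a primary aim.

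**Conclusion.** The concern holds as a risk that the stated rule leaves open, not as a demonstrated error in how the folds will be formed. At the plan's own figures, a model with no stress information can show a balanced error rate of about 0.17–0.22 if 0.48 is the ICC of the binary outcome, or 0.25–0.33 if it is on the latent scale, against about 0.50 with participant-level folds. For stress-only machine learning the corresponding range is about 0.42–0.50.

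These sizes assume record-level folds, predictions that use the participant's random intercept (for the first two ranges), a beta or normal distribution of participant effects, cuts at 0.25 or 0.5, and an assumed stress ICC of 0 to 0.7 for the random forest.

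**What to change.** In Statistical analyses, state that:
- folds are formed by participant, all records of a participant are in the same fold, and test predictions do not use that participant's outcomes; or, if personalised prediction is the target, each person's earlier days are used for training and later days for testing;
- the same performance measure is reported for the same model without stress;
- the Aim 2 conclusion rests on the difference between the two;
- the measure is the balanced error rate or the raw percentage misclassified, whichever is meant.

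Splitting stress into a person mean and a deviation from it is an optional modelling refinement and is not needed to close this gap.

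The cost is a few sentences, a grouped-fold option in the code and no new data. About 15% of the sample had completed the study when the article was written, so the rule can be set before analysis. The reported performance will probably look less favourable. Test folds of 100 / 5 = 20 people are also noisier, which repeating the cross-validation over several random partitions reduces.
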